## Abstract

**Objective:**

(1) This trial will compare the clinical and psychosocial effectiveness of in-group and individually pain neuroscience education (PNE) in patients with chronic low back pain (CLBP). In addition, (2) the influence of social determinants of health on post-treatment results will be analyzed.

**Methods:**

A three-arm randomized controlled trial will be conducted. Sixty-nine participants with CLBP will be recruited in a 1:1:1 ratio. Participants, assessor, and statistician will be blinded to group assignment. The PNE intervention will be adapted to the context of the participants. An experimental group (*n* = 33) will receive PNE in an in-group modality, the other experimental group (*n* = 33) will receive PNE in an individually modality and the control group (*n* = 33) will continue with usual care. Additionally, participants will be encouraged to stay active by walking for 20–30 min 3–5 times per week and will be taught an exercise to improve transversus abdominis activation (bracing or abdominal following). The outcome measures will be fear avoidance and beliefs, pressure pain threshold, pain self-efficacy, catastrophizing, pain intensity, and treatment expectation. Outcome measures will be collected at one-week before intervention, immediately post-intervention, and four-weeks post-intervention.

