#### Sample size

Sample size calculation was performed with G*Power 3.1. A repeated measures analysis of variance (ANOVA) model with within-between interaction, was used. Assuming an alpha risk of 0.05, a power of 0.95, a correlation between repeated measures of 0.5, a 10% drop-out rate, and a small effect size (0.26), a total of 20 participants per group (three groups) were required. The effect size estimate was based on a previous study about education compared to physical therapy for the FABQ outcome (Marshall et al., 2022) and the recommended effect size for clinical studies (Lakens, 2013).

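### The abstract gives two incompatible enrolment totals (69, and 33 per arm = 99), and the sample-size section's 20 per group matches neither as written

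*Protocol article*

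**What the plan says.** Three figures bear on the size of the trial.

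- **Abstract, Methods, total:** "Sixty-nine participants with CLBP will be recruited in a 1:1:1 ratio".
- **Abstract, Methods, by arm:** for the third arm the text reads "the control group (*n* = 33) will continue with usual care". The two education arms, group and one-to-one, each carry the same figure of 33.
- **Sample size section:** "a total of 20 participants per group (three groups) were required". Error rates are set by "Assuming an alpha risk of 0.05, a power of 0.95". The section also fixes ρ at 0.5, and its remaining inputs are "a 10% drop-out rate, and a small effect size (0.26" on G*Power's scale, for the interaction term of a repeated measures ANOVA.

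The number of repeated measurements entered in G*Power is not given. Data collection and management lists three assessments. The Statistical approach section describes the time factor of the two-way ANOVAs as pre-post, which suggests two.

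**The concern.** A fixed-sample trial needs one number at which recruitment ends, and the article does not supply one. The total and the arm sizes in the abstract disagree by 30 participants (99 − 69), within the same paragraph. The section that should settle the matter gives a third figure and leaves unclear whether drop-out is already in it.

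Two things depend on the answer. One is the planned length of the permuted-block allocation list. The other is the precision of the comparison the trial is built around, in-group against individual delivery, which the analysis reaches through Bonferroni-corrected pairwise t-tests.

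**Working it through.** **1. The totals.** At 1:1:1, 69/3 = 23 per arm. The arm sizes give 3 × 33 = 99. The sample-size section gives 3 × 20 = 60. So 99 is 43% more than 69 (30/69) and 65% more than 60 (39/60).

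**2. Reproducing the 20 per group.** Inputs from the Sample size section: k = 3 groups, effect size 0.26, correlation ρ = 0.5, alpha 0.05, target power 0.95. Assumptions: 0.26 is Cohen's f in G*Power's default convention, and sphericity holds. The number of measurements m is not stated, so both 2 and 3 are run.

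λ = f² × N × m / (1 − ρ), with df1 = (k − 1)(m − 1) and df2 = (N − k)(m − 1). Power comes from the noncentral F distribution.

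- m = 2, N = 60: λ = 0.0676 × 60 × 2 / 0.5 = 16.22, df 2 and 57, power 0.949. The smallest N reaching 0.95 is 61, or 63 when balanced (21 per arm), before drop-out.
- m = 3, N = 60: λ = 0.0676 × 60 × 3 / 0.5 = 24.34, df 4 and 114, power 0.984. The smallest N reaching 0.95 is 49, or 51 when balanced (17 per arm). With 10% drop-out, 17/0.9 = 18.9, so 19 per arm (57).

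Twenty per group is therefore about right, either as a figure before drop-out with two measurements (0.949 against 0.95) or as a figure after drop-out with three (20 against 19).

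**3. Linking 60 to 69.** If 20 is the evaluable number, 20/0.9 = 22.2, rounded up to 23, and 3 × 23 = 69. This works exactly, but the section counts the drop-out among the inputs that led to 20, so the link is an inference.

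**4. Linking anything to 99.** The stated inputs give at most 21 per arm before drop-out and 24 after it (21/0.9 = 23.3, m = 2). Neither value of m gives 33.

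**5. What the choice of total changes.** The half-width is for a difference between two arms at one time point: 1.96 × √(2/n) in SD units, normal approximation, no drop-out, no multiplicity correction.

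| Total (per arm) | Power, m = 2 | Power, m = 3 | 95% half-width |
|---|---|---|---|
| 60 (20) | 0.949 | 0.984 | 0.62 SD |
| 69 (23) | 0.973 | 0.994 | 0.58 SD |
| 99 (33) | 0.997 | 0.9998 | 0.48 SD |

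If 60 are enrolled and 10% are lost (54 evaluable), power is 0.924 for m = 2 and 0.971 for m = 3.

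**The case against.** The best defence is that one slip and one ambiguity explain everything. The Sample size section speaks of the number required and the abstract of the number recruited. These are different quantities, and 20 evaluable leads to 23 recruited and 69 in total. On that reading 33 is a misprint for 23, which would have been repeated for all three arms. A full trial protocol is also listed as a supplement that is not shown here, and it may state the target correctly.

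Much of this stands. The 60 is not a proven third target, and the firm contradiction is 69 against 99. But the article states neither repair. A reader cannot tell which abstract figure is the slip. Nor is 33 obviously meaningless: the same formula family gives 99 for a different test (the between-groups main effect, three measurements, power 0.80). That is not the calculation the article describes, but it is a reason not to assume a misprint. Condensing a protocol into an article does not explain two totals in one paragraph.

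Three stronger readings are tempting and are not supported:

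- **That 20 per group is a miscalculation.** It is reproduced to within one per arm under either number of measurements.
- **That the trial is underpowered.** The interaction test keeps 0.92 at worst.
- **That recruitment might be stopped according to the results.** No interim look is described, and the assessor and statistician are to be blinded.

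**Conclusion.** The point holds. The abstract contradicts itself on enrolment (69 against 99), and the sample-size section, as worded, agrees with neither figure. The figure of 20 per group is roughly supported by its inputs and can be tied to 69 if it is a number before drop-out. The figure of 33 per arm cannot be derived from those inputs.

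The consequence is limited but real. The article gives no single recruitment target, and the 95% half-width for a pairwise arm contrast could be anything from 0.48 to 0.62 SD. The power results rest on reading 0.26 as Cohen's f in G*Power's default convention, on sphericity, and on two or three measurements. The contradiction in the totals rests on no assumption. It should be corrected because the sample size is a figure the whole trial relies on and the correction costs almost nothing.

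**What to change.** State one total and one per-arm number wherever the size of the trial appears.

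- **If 69 is intended:** change each n = 33 in the abstract to n = 23, and reword the Sample size section to say 20 evaluable per group, 23 randomised per group (69 in total), to allow for 10% drop-out.
- **If 33 per arm is intended:** change the abstract's total to ninety-nine and give the calculation that supports it.

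In either case, state the number of measurements entered in G*Power. If it was two, 20 evaluable gives 0.949, so the power should be described as approximately 0.95.

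The cost is a wording correction in the abstract and one section. Confirming 69 needs no additional participants. Confirming 99 means 30 more than the abstract's stated total, plus a justification.

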**Conclusion:**

The innovative approach of PNE oriented to fear beliefs proposed in this study could broaden the application strategies of this educational therapeutic modality. Impact. Contextualized PNE delivered by physical therapist could be essential to achieve a good cost-effectiveness ratio of this intervention to improve the clinical condition of people with CLBP.

## Introduction

Chronic low back pain (CLBP) is the leading cause of disability worldwide (Hoy et al., 2010). It has been shown that approximately 67% of the general population have low back pain for more than three months (Itz et al., 2013). The disability in these individuals varies from 11% to 76% (Côté et al., 2008; Wynne-Jones, Dunn & Main, 2008), with a significant impact of psychosocial factors on their response to treatment (Hill & Fritz, 2011; Alhowimel et al., 2018). Furthermore, social determinants of health (SDH) are a determining factor on the symptomatology of CLBP (Karran, Grant & Moseley, 2020), associated with substantial social and healthcare expenses (Luo et al., 2004).

The psychological factors of the fear-avoidance model, such as catastrophizing, beliefs, fear of movement, and self-efficacy, are important determinants of symptom perception and disability. These psychological factors can impede the recovery process (Pincus et al., 2002b; Pincus et al., 2002a; Leeuw et al., 2007; Zale & Ditre, 2015), cause physical deconditioning, and perpetuate pain in people with CLBP (Vlaeyen & Linton, 2000). From this perspective, catastrophizing shows a moderate correlation with pain intensity and disability in patients with CLBP (Meyer et al., 2009). It is also a significant predictor of both pain intensity and disability (Picavet, Vlaeyen & Schouten, 2002). Furthermore, fear avoidance and self-efficacy beliefs predict disability and mediate the disability-pain intensity relationship (Denison, Åsenlöf & Lindberg, 2004; Woby, Urmston & Watson, 2007; Costa et al., 2011; Lee et al., 2015), making them potential targets for clinical interventions (Pincus et al., 2002a). In this sense, it has been shown that the management of avoidance beliefs has an effect in reducing disability and pain in patients with CLBP (Wertli et al., 2014), and high levels of self-efficacy may prevent the vicious cycle of deconditioning and pain perpetuation (Woby et al., 2004). Furthermore, it has been found that there are independent and interdependent relationships between SDH and CLBP mainly for educational level and socioeconomic level (Karran, Grant & Moseley, 2020).

In chronic pain rehabilitation, it is essential to address the factors mentioned above (McCracken, 2005). In this sense, the biomedical approach to education may promote the fear-avoidance model (Louw et al., 2011), while the pain neuroscience education (PNE) promotes patients’ understanding of chronic pain and changes maladaptive thoughts and cognitions (Moseley, 2002; Meeus et al., 2010) with a biopsychosocial approach limiting the fear-avoidance model (Louw et al., 2016b). PNE has shown positive results on the kinesiophobia, catastrophizing, pain intensity, disability, and physical performance in patients with CLBP (Moseley, Nicholas & Hodges, 2004; Ryan et al., 2010; Louw et al., 2011; Malfliet et al., 2017; Rufa, Beissner & Dolphin, 2018; Núñez Cortés et al., 2023a; Nuñez Cortés et al., 2023b). A recent meta-analysis has shown that the in-group PNE had better results than individual PNE for kinesiophobia (Romm et al., 2021), and it has been identified, in other types of health education, that there are greater benefits in those people who received the in-group intervention (Riemsma, Taal & Rasker, 2003), probably supported by the fact that educational sessions conducted in-group modality can facilitate learning through social observation of positive behaviors exhibited by other members within the group (Romm et al., 2021; Salazar-Méndez et al., 2024). However, there are no primary studies comparing the two PNE modalities directly. On the other hand, despite increasing evidence that SDH are influential factors in clinical health outcomes to a greater extent than the quality and availability of medical care (Daniel, Bornstein & Kane, 2018), there are no studies that analyze specifically the influence of SDH factors (*e.g.*, educational level) on the effectiveness of PNE (Salazar-Méndez et al., 2024).

We hypothesize that there will be significant differences in favor of the intervention in-group modality compared to the individual modality. Furthermore, the effects will be influenced by the social determinants of health in both experimental groups.

### Study objectives

The objectives of this trial are: (1) to compare the clinical and psychosocial effectiveness of in-group modality and individual modality of pain neuroscience education (PNE) in patients with CLBP; (2) To analyze the influence of social determinants of health on post-treatment results.

## Methods

### Study design

This randomized controlled trial study protocol has a three-group comparison design, with a control group, individual intervention group, and in-group intervention group. It has been designed according to the Standard Protocol Items for Randomized Interventional Trials (SPIRIT) (Chan et al., 2013), the CONSORT guidelines (Schulz, Altman & Moher, 2010) (Fig. 1), and the Template for Intervention Description and Replication (TIDieR) Checklist (Hoffmann et al., 2014).

**Figure 1 fig-1:**
[figure not shown]
The proposed CONSORT diagram of enrollment, allocation, follow-up, and analysis throughout the study for each arm.

The study population will be people diagnosed with low back pain for ≥ 3 months. Participants will be recruited from the clinical center of the Santo Tomás University, through social media and publications health centers in the city of Talca.

#### Ethics

The study was approved by the Central-South Macrozone Ethics Committee of the Universidad Santo Tomás, Chile, according to the Declaration of Helsinki for biomedical research (exp-23-13). All participants will provide written informed consent.

### Eligibility criteria

Inclusion criteria will be men and women aged 45–60 years (Knauer, Freburger & Carey, 2010), non-specific low back pain ≥ 3 months without compromise of any lower limb, average pain intensity ≥ 3/10 and ≤8/10 (according to the 0–10 numerical rating scale (NRS)) in the last month. Exclusion criteria will be psychiatric, neurological or oncological diseases, operated of some lumbar pathology, chronic low back pain due to a specific cause (lumbar stenosis, herniated disc, spinal deformity, fracture, spondylosis), be receiving some form of active or passive physical therapy for pain at the time of the investigation or having received it in the last two months, and have previous experiences with PNE.

### Intervention

The content of the intervention will be identical in the experimental groups. The only difference is that the PNE in the in-group modality (G1) is provided in groups of 3–5 participants, while in the individual modality (G2) it is provided directly to a single participant. The intervention has an active educational approach based on reconceptualizing the maladaptive beliefs that influence the fear-avoidance behavior of the participants through updated contents of the neuroscience of pain. This will be delivered in a single face-to-face session of approximately 60–80 min in the kinesic clinic of the Santo Tomás University and will be delivered through active participation encouraging synchronous discussion of the information and allowing note-taking. A break will be made in the middle of the session to allow the participants a break. Five key domains will be structured based on the Fear and Belief Avoidance Questionnaire (Table 1) which will serve as a guide for the sessions through a Powerpoint presentation. In addition, participants will be encouraged to stay active by walking for 20–30 min, 3–5 times a week and will be taught an exercise to improve the activation of the transverse abdominis (bracing or abdominal following). The PNE will be delivered by a physical therapist with four years of experience in this intervention. In addition, the same physical therapist will provide the therapy to both experimental groups to maintain the same patient-physical therapist relationship and not to influence the results due to this contextual aspect, so no adaptations were made for each group either.

**Table 1 table-1:** Summary content of pain neuroscience education.

**Dimension**	**Content**
Dimension 1: Approach	Introduction to the program.
	The objective of today’s session will be to contrast what we know about pain, with the scientific advances in rehabilitation through a conversation.
	Your opinion regarding each of the points that we will discuss is very important for your rehabilitation.
Dimension 2: Pain as protector (the big picture)	Pain as a multidimensional experience
	- Neurophysiology of pain: pain pathways, neuronal synapses, action potentials and pain perception. Gate of entry of pain.
	- Modulation of pain: explain the processes of facilitation and inhibition. The theory of gate control will be emphasized.
	- Acute pain and chronic pain: explain the differences between acute pain and chronic pain
Dimension 3: Pain is not always an indicator of damage (pain ≠ damage)	Pain does not depend entirely on the state of the tissues.
	Imaging findings associated with aging are like wrinkles or gray hair.
	examples of pain in the absence of damage (eg headache)
Dimension 4: Movement as an opportunity for recovery (movement experience)	-Importance of movement
	-explain the relevance of movement from the plasticity and robustness of the human body.
	-Neuroplasticity of the nervous system: Explain neuroplastic changes due to experience and learning with an emphasis on positive changes through movement.
	benefits of movement in functionality
	progressive active strategies
Dimension 5: Recovery expectations	Concept of pain modulation from cognitions
	strategies to help manage pain, relaxation/breathing techniques, positive thinking

In addition, a brochure will be delivered with the main points of each of the domains and information capsules will be made to which the participants will have access (five 15-minute videos, one per domain). Participants will be instructed to record on a calendar the days they performed the walks, exercises, and read the brochure, and/or review the information capsules to assess compliance with the treatment and for each domain invent a metaphor or write how they would explain it to another person. This activity must be delivered in the second assessment.

The total time of the intervention will be 135–155 min for both groups.

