### Data analysis

#### Statistical approach

The analysis of the data will be blinded, as each subject and condition will be coded by a consultant who will not be involved in the investigation. SPSS software version 25.0 will be used for all analyzes (SPSS Inc. Armonk, NY, USA). Data will be reported as mean with SD or median with interquartile range. Statistical analyzes were performed on an intention-to-treat basis, with imputation of missing data using the average of the remaining participants.

Normality tests will be performed using the Shapiro–Wilk test given the number of subjects needed for each group. In addition, the homogeneity of variance and the sphericity of the data will be determined. In the case of not assuming any of these assumptions, the Green-Hausser correction will be used for the interpretation of subsequent analyzes. A three-way repeated measures ANOVA will be conducted to analyze both primary and secondary outcomes. The factors considered in this analysis will include time and intervention. Additionally, the third factor will encompass variables such as employment status, education level, or income. In case of significant interaction, a two-way repeated measures ANOVA (time (pre-post) × intervention (in-group PNE, individually PNE, no intervention)) will be performed for each employment status (employed or unemployed). Furthermore, a two-way repeated measures ANOVA (time (pre-post) × intervention (in-group PNE, individually PNE, no intervention)) will be performed for each educational level (high or low). Lastly, a two-way repeated measures ANOVA (time (pre-post) × intervention (in-group PNE, individually PNE, no intervention)) will be performed for income (≤USD 545, or >USD 545). If interactions are detected in any of the 2-way ANOVAs, a *post-hoc* analysis will be conducted using multiple pairwise comparisons employing a *t*-test corrected by Bonferroni. The significance level will be set at 5%.

A stepwise multiple linear regression will be performed to estimate the influence of changes in primary and secondary outcomes. In each model, adjustments will be made for employment status, educational level, and income. In this analysis, the aforementioned variables will be sequentially incorporated into each model.

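### Only the in-group arm is treated in shared sessions of 3–5, yet the planned ANOVA and t-tests have no session term; if outcomes within a session correlate, the standard error of the in-group comparisons is too small

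*Protocol article*

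**What the plan says.** The Intervention section of the Protocol article fixes how each experimental arm is treated: the in-group version "is provided in groups of 3–5 participants, while in the individual modality (G2) it is provided directly to a single participant". Each participant attends once: "This will be delivered in a single face-to-face session of approximately 60–80 min". The session is interactive and "will be delivered through active participation encouraging synchronous discussion of the information". One physical therapist treats both experimental arms.

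The Introduction explains why a group might do better: such sessions "can facilitate learning through social observation of positive behaviors exhibited by other members within the group". The Discussion repeats the idea. The Introduction also names the contrast of main interest: "We hypothesize that there will be significant differences in favor of the intervention in-group modality compared to the individual modality".

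Under Statistical approach, "A three-way repeated measures ANOVA will be conducted to analyze both primary and secondary outcomes". Its factors are time, intervention and one social determinant. Two-way repeated-measures ANOVAs follow, and then Bonferroni-corrected pairwise t-tests if an interaction is found. None of these has a term for session. The Sample size section uses one correlation, 0.5, which is between repeated measures on the same person and not between people who share a session.

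**The concern.** People in the same session hear one conversation and help to shape it. If one session goes well and another badly, the members of each shift together and their outcomes correlate. The in-group arm then carries less information than its head count suggests, while the individual and control arms do not. This is a partially nested design.

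The named ANOVA and t-tests assume independent participants. Under positive within-session correlation they understate the variance of the in-group mean, so intervals for both in-group contrasts are too narrow and their p-values too small. One of these contrasts is the trial's stated hypothesis, and the Introduction says that no primary study has yet compared the two formats directly, so later users will rely on this standard error. The article names the model, its factors and the post-hoc test; the point concerns that stated choice and not a detail left to another document.

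**Working it through.** **Inputs from the Protocol article.** Session size m = 3–5 in the in-group arm and 1 in the individual arm (Intervention). Alpha 0.05, power 0.95, repeated-measures correlation 0.5, effect size f = 0.26, 10% drop-out, 20 per group (Sample size). Three measurement times (Data collection and management). The arm size is inconsistent: the Abstract gives 69 in total (23 per arm at 1:1:1) and also 33 per arm, against 20 under Sample size. All three sizes are carried through.

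**Assumed.** The within-session ICC, because none is given: 0.01 to 0.20.

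**Step 1: the plan's own figure.** For the within-between interaction, λ = f²·N·T/(1 − ρ), with df1 = (k − 1)(T − 1) and df2 = (N − k)(T − 1). With k = 3 groups, T = 3 times and N = 51, λ = 0.0676 × 51 × 3 / 0.5 = 20.7, df are 4 and 96, and power is 0.961 (N = 48 gives 0.949). Allowing for drop-out, 51/0.9 = 56.7, so 57, or 19 per group against the stated 20. The figure is reproduced to within one person per group by a formula that treats all participants as independent.

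**Step 2: standard error.** The design effect in the in-group arm is DE = 1 + (m − 1)·ICC; in the other arms it is 1. With equal arms, true SE / naive SE = √((DE + 1)/2). For m = 4 and ICC = 0.10: DE = 1 + 3 × 0.10 = 1.30, and √(2.30/2) = 1.072.

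| ICC (assumed) | DE, m = 3 / 4 / 5 | SE ratio, m = 3 / 4 / 5 |
|---|---|---|
| 0.01 | 1.02 / 1.03 / 1.04 | 1.005 / 1.008 / 1.010 |
| 0.05 | 1.10 / 1.15 / 1.20 | 1.025 / 1.037 / 1.049 |
| 0.10 | 1.20 / 1.30 / 1.40 | 1.049 / 1.072 / 1.095 |
| 0.20 | 1.40 / 1.60 / 1.80 | 1.095 / 1.140 / 1.183 |

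The same ratio applies to in-group versus control. With sessions of 4, 20 participants carry the information of 20/DE = 17.4, 15.4 and 12.5 independent ones at ICC 0.05, 0.10 and 0.20.

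**Step 3: type I error of the planned sequence.** This was simulated as a single-outcome simplification: three arms with no true difference, clusters in one arm only, an omnibus F test at 5%, then Bonferroni over three pairs (0.05/3 = 1.7%). The ranges cover sessions of 3–5 and 20, 23 or 33 per arm.

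| ICC (assumed) | Omnibus F (nominal 5%) | In-group vs individual, after the F test, Bonferroni (nominal 1.7%) |
|---|---|---|
| 0.05 | 5.5–6.0% | 1.7–2.0% |
| 0.10 | 5.8–7.1% | 2.0–2.6% |
| 0.20 | 7.0–9.7% | 2.5–4.0% |

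A normal approximation for the Bonferroni test without the preceding F test agrees. Its critical value is 2.394; with m = 4, dividing by 1.037, 1.072 and 1.140 gives two-sided errors of about 2.1%, 2.6% and 3.6%. Simulating the three-group by three-time interaction test itself, with 20 per arm and a session effect on both post-treatment measurements, gives 5.6–6.0%, 6.2–7.0% and 8.1–10.3%.

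**Step 4: number of sessions.** From 20/5 = 4 to 33/3 = 11, depending on arm and session size.

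**The case against.** The strongest reply is that the correlation may be small. There is one session of 60–80 minutes, its content is the same in both experimental arms and guided by slides, and a single therapist delivers it, so there is no between-therapist component. The five 15-minute videos account for 75 of the stated 135–155 minutes, about half, and are given as material to view outside the session. The social-learning argument is worded tentatively and concerns an average benefit; a benefit equal in every session would create no between-session variance. All of this stands. It makes the ICC 0.20 row the least supported by the article, and near ICC 0.01 the problem is negligible. It does not make independence a safe default where discussion among members is part of the treatment.

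Three stronger readings are tempting, and the article does not support them.

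- A reader might infer that the standard error is certainly too small. That holds only if the ICC is positive, and no value is given.
- A reader might quote the error of an ordinary 5% t-test between the two experimental arms: at 23 per arm and sessions of 4, about 5.7%, 6.6% and 8.5% at ICC 0.05, 0.10 and 0.20. That is not the planned test. Pairwise tests are run only after a significant interaction and are Bonferroni-corrected, and in the simulation their error for this contrast stays below 5% throughout. It still exceeds its nominal 1.7% at ICC 0.10 and above, and the omnibus test is inflated too.
- A reader might infer that the estimate itself favours the in-group arm. It does not: the difference is unbiased, and false positives arise in both directions.

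**Conclusion.** The concern holds as a conditional point about precision. The analysis named in the article does not match the delivery it describes, and its own rationale gives a reason to expect positive within-session correlation. At ICC 0.05–0.10 the true standard error of the in-group contrasts is about 2–10% larger than the one the plan would report, and the omnibus error is roughly 6–7% instead of 5%. At ICC 0.20 the figures reach 10–18% and 7–10%; at ICC 0.01 they are trivial. The type I error figures come from a simplified single-outcome simulation. The conclusion is the same for 20, 23 or 33 per arm, so the conflict over sample size, a separate matter, does not affect it. The change should be made, because the correction is simple and session membership may not be recoverable if it is not recorded during the trial.

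**What to change.** Record a session identifier for every in-group participant. Replace the ANOVA by a partially nested mixed model: a random session effect in the in-group arm only, with each individual-arm and control participant as a cluster of one; repeated measures within person; and Satterthwaite or Kenward–Roger degrees of freedom. Take the Bonferroni-adjusted pairwise contrasts from this model in place of separate t-tests. Report the ICC with its interval.

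The cost is one data field and one model term, but also some precision. Intervals for the in-group contrasts will widen. With only about 4–11 sessions, the session variance and the ICC will be poorly estimated, and the small-sample degrees of freedom cost power beyond the design effect. As a guide when the sample-size figures are reconciled: to keep the information of 20 independent participants at ICC 0.10, the in-group arm needs 24–28 (20 × 1.20 to 20 × 1.40); to keep that of 33 it needs 40–47 (33 × 1.20 = 39.6 to 33 × 1.40 = 46.2, rounded up).
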